### Secondary endpoints

- Patient stress during Injection Visit #2, estimated by changes in HRV, measured before and during the botulinum toxin injection session using the LF/HF ratio.
- Pain intensity experienced by the patient during Injection Visits #1 and #2, measured immediately after the injection session using a simple Numerical Rating Scale (NRS) ranging from 0 (“no pain”) to 10 (“worst imaginable pain”).
- Anxiety variation measured by the self-administered State-Trait Anxiety Inventory - Form Y, State subscale (STAI-Y1) during Injection Visits #1 and #2, before and after the botulinum toxin injections. The STAI-Y1 consists of 20 items rated on a 4-point Likert scale, from 1 (“Not at all”) to 4 (“Very much”) (see ANNEX 2).
- Patient’s perception of the duration of the session relative to the actual injection time during Injection Visits #1 and #2. This self-reported data will be collected at the end of each session.
- Patient satisfaction with the intervention assessed using a Visual Analog Scale (VAS) ranging from 0 (“no satisfaction”) to 10 (“highest satisfaction”), measured after the injections during Visits #1 and #2.
- Quality of the botulinum toxin injection conditions, as assessed by the physician immediately after each session during Visits #1 and #2, using a simple Numerical Rating Scale (NRS) from 0 (“extremely poor conditions”) to 10 (“extremely good conditions”).

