## Primary analysis

The primary objective of this study is to assess the effect of exposure to a music intervention session during the botulinum toxin injection visit #1 on the stress induced by the injection. The primary analysis will rely on a Student's t-test or a Mann-Whitney test, comparing the variation in heart rate variability (HRV) (using the LF/HF ratio) between the randomized groups.

The validity conditions will be verified both graphically and statistically. The equality of variances will be assessed using the Fisher-Snedecor test. The results will be expressed in terms of effect sizes and 95% confidence intervals.

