## Secondary analyses

The main analysis may be supplemented by a multivariate analysis using multiple linear regression to account for covariates selected based on univariate analysis results and their clinical relevance (including sex and age of the patients). Special attention will be given to the study of multicollinearity (Farrar and Glauber test and VIF indicator). The validity of the model (normality of residuals and homogeneity of variances) will be visually assessed. The results will be expressed in terms of regression coefficients, effect sizes, and 95% confidence intervals.

Subgroup analyses will be conducted for the primary endpoint, based on the sex and age of the patients. The interaction between group and subgroup will be explored. The results will be expressed in terms of regression coefficients, effect sizes, and 95% confidence intervals.

Analyses aimed at studying the effect of exposure to a music intervention session during botulinum toxin injections at visit #1, in terms of stress induced by the injection for HRV parameters other than LF/HF, pain induced by the injection, anxiety during the injections, patient satisfaction, and the effect of music intervention on the medical procedure (botulinum toxin injections) as expressed by the physician at the end of the session, will follow the same statistical analysis plan as for the primary endpoint.

Analyses to study the effect of exposure to a music intervention session at visit #2 (to evaluate the effect of repeated exposure to a music intervention) on the variation of stress, pain, variation of anxiety, patient satisfaction, and the effect of music intervention on the medical procedure (botulinum toxin injections) as expressed by the physician at the end of the session, will rely on mixed models.

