Specifically, the study of longitudinal repeated data will be performed using random-effects models, which allow for the study of fixed effects (groups, evaluation time, and their interaction) while accounting for inter- and intra-patient variability. To compare between randomized groups, the means of the quantitative criteria evaluated at visits #1 and #2 will be analyzed using a mixed linear model of constrained Longitudinal Data Analysis (cLDA). In this model, the dependent variable includes both values at visit #1 and post-inclusion values, and the mean difference at visit #1 between groups is constrained to 0. This model allows the calculation of changes between visit #1 and each follow-up time point (here, visit #2), while adjusting for values at visit #1. The difference between groups is obtained through the interaction between time and the randomization group. The model will include different random effects at the patient level (a model with random intercepts and slopes, allowing for variation between patients in both baseline values and changes in the outcome over time). The model parameters will be estimated using the restricted maximum likelihood (REML) method. Intra-group randomization analyses will also be performed.

For categorical criteria, a generalized linear mixed model with logit link of the type cLDA (constrained Longitudinal Data Analysis) will be considered. In this model, the dependent variable includes both inclusion and post-inclusion values, and the event difference between the two groups is constrained to 0. This model allows for the calculation of odds ratios at each follow-up time point (visit #2), adjusting for values at visit #1. The subject effect will be treated similarly to what was previously described.

Comparisons between randomized groups not involving repeated data will use conventional statistical tests: (1) Student's t-test or Mann-Whitney test if t-test assumptions are not met (normality and homoscedasticity assessed using the Fisher-Snedecor test) (e.g., for patient satisfaction) and (2) Chi-squared test or, if applicable, Fisher's exact test.

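### The visit 2 satisfaction model sets a post-randomisation visit 1 difference to zero, and section 10.4 is ambiguous about which method applies to satisfaction

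*Protocol*

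**What the plan says.** Section 6.1.2 defines satisfaction as a 0-10 visual analogue rating, "measured after the injections during Visits #1 and #2". It is therefore a quantitative criterion recorded twice, each time after the session.

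Sections 10.3 and 10.4 give it these analyses:

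- **Visit 1.** Satisfaction is among the outcomes that "will follow the same statistical analysis plan as for the primary endpoint". For that endpoint, section 10.3 states: "The primary analysis will rely on a Student's t-test or a Mann-Whitney test".
- **Visit 2.** Satisfaction is named in the list of effects "on the variation of stress, pain, variation of anxiety, patient satisfaction, and the effect of music intervention on the medical procedure", which, "as expressed by the physician at the end of the session, will rely on mixed models".
- **General rule for both visits.** Section 10.4 adds that "the means of the quantitative criteria evaluated at visits #1 and #2 will be analyzed using a mixed linear model". The model is a constrained longitudinal data analysis (cLDA): visit 1 values are part of the response, the arm difference at visit 1 is fixed at zero, and the arm effect is read from the time-by-group interaction.
- **Rule for non-repeated data.** Section 10.4 then says "Comparisons between randomized groups not involving repeated data will use conventional statistical tests", meaning Student or Mann-Whitney for quantitative data, with the example "e.g., for patient satisfaction". No visit is given.

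Under section 7.1, at visit 1 the CT-IM arm has usual practice with the heart rate belt and the IM-IM arm has music. Both arms rate their satisfaction afterwards. At visit 2 both arms have music.

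**The concern.** There are two problems, of unequal weight.

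The lesser one is wording. The only example of non-repeated data is an outcome that sections 6.1.2 and 10.4 otherwise treat as repeated. An analyst could cite the example for a two-sample test at visit 2, or the visit 2 list for the mixed model.

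The greater one is the model. Fixing the arm difference at zero is justified for a measurement taken before randomised treatment, because randomisation makes the two means equal in expectation. Visit 1 satisfaction is not such a measurement. It is collected after the randomised session, and the CT-IM patients had no music to be satisfied with. If music raises satisfaction at visit 1, which the trial sets out to test, the constraint is false, and the model pushes the visit 1 effect into the visit 2 contrast with its sign reversed. Repeated exposure could then look harmful when it does nothing, or a real visit 2 benefit could be hidden.

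**Working it through.** **The plan's own figure.** The protocol gives no figure for satisfaction. Its only sample size figure concerns LF/HF (section 10.1: difference 1.8, SD 2.3, two-sided 5%, power 90%). It reproduces: n = 2 × (1.960 + 1.282)² × 2.3² / 1.8² ≈ 34.3, so 35 per arm. Nothing below depends on it except the planned 40 per arm.

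**Inputs.** From the protocol: 40 per arm, 1:1 allocation, two ratings per patient, visit 1 difference fixed at 0. Assumed, because the protocol does not give them: SD 2.0 at both visits, visit 1 effect d1 of 0 to 2 points, within-patient correlation ρ of 0.3 to 0.7, true visit 2 difference d2 of 0 unless stated.

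**Formula.** With complete data, the constrained model's visit 2 contrast equals the estimate from regressing visit 2 on arm and visit 1. A direct maximum-likelihood fit to one simulated dataset confirmed this: both gave -0.624, against a raw visit 2 difference of 0.129. The expected value is

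d2 - β × d1, with β = ρ × SD2/SD1 = ρ when the SDs are equal.

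A two-sample comparison at visit 2 has expected value d2.

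With d2 = 0, the smallest shift for d1 of 1 to 2 is -0.3 × 1 = -0.3 and the largest is -0.7 × 2 = -1.4 points.

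**Simulation.** 4000 runs per row, 40 per arm, d2 = 0; rejection at two-sided 5%.

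| d1 | ρ | Two-sample estimate | Rejects | Constrained estimate | Rejects | Differ on significance |
|---|---|---|---|---|---|---|
| 0 | 0.3 | -0.01 | 5% | -0.01 | 5% | 3% |
| 0 | 0.5 | 0.00 | 5% | 0.01 | 6% | 5% |
| 0 | 0.7 | 0.01 | 5% | 0.00 | 5% | 7% |
| 1.0 | 0.3 | 0.00 | 5% | -0.30 | 10% | 9% |
| 1.0 | 0.5 | -0.01 | 5% | -0.51 | 25% | 24% |
| 1.0 | 0.7 | 0.01 | 5% | -0.69 | 54% | 54% |
| 1.6 | 0.3 | 0.00 | 5% | -0.48 | 18% | 18% |
| 1.6 | 0.5 | 0.00 | 5% | -0.80 | 46% | 46% |
| 1.6 | 0.7 | -0.01 | 5% | -1.12 | 89% | 88% |
| 2.0 | 0.3 | 0.00 | 5% | -0.61 | 23% | 22% |
| 2.0 | 0.5 | 0.01 | 5% | -0.99 | 61% | 61% |
| 2.0 | 0.7 | 0.01 | 5% | -1.39 | 97% | 94% |

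**Masking.** With a true visit 2 benefit of 1 point, d1 = 1.6 and ρ = 0.5, the expected constrained estimate is 1 - 0.5 × 1.6 = 0.2. It is significant in 7% of runs, against 59% for the two-sample test.

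**The case against.** A reader might infer that section 10.4 assigns two competing analyses to satisfaction at visit 2. The text does not support that. The example names no visit, and the only method expressly assigned to visit 2 satisfaction is the mixed model; section 6.3 likewise points to mixed models for the visit 2 comparison. Read as the visit 1 comparison, the example only repeats the Student or Mann-Whitney test already given for visit 1. Repetition is not contradiction. It is a somewhat awkward reading, since pain and the physician's rating are also single post-session scores and are not mentioned, but it is available. This part of the objection stands.

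It is also fair that the size comes from the constraint and not from the ambiguous example. Adding a visit to the example would settle the wording and leave the bias. The same reasoning reaches the other outcomes in the visit 2 list, since they too are affected by the visit 1 session. That limits what a change to satisfaction alone achieves, but does not make the model suitable for satisfaction.

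Finally, the visit 1 effect and correlation are assumptions, and with no visit 1 effect both methods estimate about 0. A separate statistical analysis plan could name the visit. The zero constraint, however, is written into the protocol itself.

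**Conclusion.** The point holds as an unsuitable model together with an ambiguous example. Following section 10.4 shifts the visit 2 satisfaction contrast by about -ρ × d1: -0.3 to -1.4 points on the 0-10 scale for a visit 1 effect of 1 to 2 points and a correlation of 0.3 to 0.7, with equal variances. Both ranges are assumed. With no visit 1 effect the shift is about 0. The direction needs no assumption beyond a positive correlation and a visit 1 benefit of music.

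The consequence is limited. Section 10.2 makes the secondary analyses exploratory, without correction of the type I error. The primary analysis is made at visit 1 on LF/HF, and neither it nor the sample size is touched.

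**What to change.** In section 10.4:

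1. Remove satisfaction from the list of visit 2 outcomes analysed by mixed models.
2. Exempt it from the general cLDA rule for quantitative criteria evaluated at both visits; otherwise that sentence still captures it.
3. State that the arms are compared on satisfaction separately at visit 1 and at visit 2 with the two-sample method already described, and name both visits in the example. A mixed model without the visit 1 constraint is equivalent, provided that the reported contrast is the arm difference at visit 2. The time-by-group interaction of that model would be d2 - d1, which is not the visit 2 difference.
4. Keep the within-group comparison of visit 1 with visit 2 as a separate analysis, since section 6.3 gives within-patient change as a purpose of visit 2.

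The cost is a wording change and some precision on an exploratory endpoint. The precision is lost only where the constraint would have been true. In that case the constrained model's standard error is smaller by a factor of about √(1 - ρ²): 0.95, 0.87 and 0.71 at correlations 0.3, 0.5 and 0.7. In the simulations with no visit 1 effect and a 1-point visit 2 difference, power is 58-60% for the two-sample test against 63%, 70% and 86%. The loss is small at low correlation and larger at 0.7, and buys an estimate that does not depend on music having had no effect at visit 1.

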# STATISTICAL CONSIDERATIONS

## Number of subjects to include

To investigate the effect of exposure to a music intervention session during botulinum toxin injections on injection-induced stress at injection visit #1, 35 patients per group are required to detect an absolute difference in HRV variation, specifically for the LF/HF ratio, of at least 1.8 with a standard deviation of 2.3, assuming a two-sided type I error rate of 5% and a statistical power of 90%.

The assumptions regarding the expected difference and standard deviation were based on a previous study conducted by our team (Clinical Trials NCT05364203).

More specifically, a difference of 1.8 with a standard deviation of 2.3 for the LF/HF ratio corresponds to an effect size of approximately 0.8, which can be considered large and clinically relevant according to Cohen’s guidelines. Our institution has conducted several studies where this outcome measure was used; effect sizes between 0.5 and 1 have generally been observed, corresponding to differences of 1 to 2 points in the LF/HF ratio. In the Clinical Trials NCT05364203 study investigating the effect of virtual reality, a difference of 1.8 points was demonstrated.

Ultimately, it is proposed to include 40 patients per group to account for potentially unusable data for the primary outcome measure and to ensure sufficient statistical power

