## Data analysis: general aspects

The statistical analyses will be conducted using Stata software (version 15, StataCorp, Texas, USA).

Continuous variables will be presented as mean and standard deviation or median and interquartile range, depending on their statistical distribution. The normality of continuous variables will be assessed using the Shapiro-Wilk test and the density curve. Categorical variables will be expressed as counts and percentages. Graphical representations will be provided whenever possible alongside the analyses.

The randomized groups will be compared at injection visit #1 according to the following variables: adherence to inclusion criteria, epidemiological characteristics, clinical characteristics, and treatments.

The initial comparability of the randomized groups will be evaluated based on key participant characteristics and potential factors associated with the primary outcome measure. Any differences between the groups on these characteristics will be determined based on clinical considerations, not solely statistical ones.

A description of protocol deviations, patients allocated based on these deviations, and reasons for withdrawal will also be provided. The number of enrolled patients and the enrollment curve will be presented by group.

The statistical analyses will first be performed according to the intention-to-treat (ITT) principle, including all patients except those who withdrew consent for the use of their data. A per-protocol analysis will be conducted by excluding patients who were not managed according to their assigned randomization group or who had major protocol deviations.

Comparisons between randomized groups will be conducted systematically (1) without adjustment and (2) with adjustment for factors that may have been imbalanced between the groups despite randomization.

The risk of a type I error will be set at a two-sided 5%. The analyses for secondary objectives will be exploratory in nature, and therefore, no correction for type I error will be applied.

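### The primary test is left as Student or Mann-Whitney after checks on the trial data, with no unequal-variance t-test, so unequal spread leads to a test that does not address the 1.8-point mean difference

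*Protocol*

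**What the plan says.** - **Section 10.3, Primary analysis.** Two candidate tests are named: "The primary analysis will rely on a Student's t-test or a Mann-Whitney test, comparing the variation in heart rate variability (HRV". The choice follows checks on the trial data: "The validity conditions will be verified both graphically and statistically", and "The equality of variances will be assessed using the Fisher-Snedecor test". Results are to be given as effect sizes with 95% confidence intervals.
- **Section 10.2, general aspects.** "The normality of continuous variables will be assessed using the Shapiro-Wilk test and the density curve".
- **Section 10.4, Secondary analyses.** For comparisons without repeated data, with patient satisfaction as the example, the switch is explicit: "Mann-Whitney test if t-test assumptions are not met (normality and homoscedasticity assessed using the Fisher-Snedecor test". The visit 1 secondary endpoints "will follow the same statistical analysis plan as for the primary endpoint".
- **Section 10.1, sample size.** The trial is sized on "an absolute difference in HRV variation, specifically for the LF/HF ratio, of at least 1.8 with a standard deviation of 2.3", at two-sided 5% and 90% power.

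No section names a t-test that allows unequal variances.

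**The concern.** The single confirmatory test is chosen after looking at the outcome data. Part of the check is graphical and no cut-off is given, so two analysts could pick different primary tests from the same data.

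The variance check also has the wrong consequence. Section 10.3 offers only two tests, so a failed Fisher-Snedecor test can only lead to Mann-Whitney. Mann-Whitney compares ranks. When the arms differ in spread, it tests neither equality of means nor, without a pure shift, equality of medians. The rule therefore changes the question in the very case it is meant to handle, and moves away from the mean difference that justifies the sample size.

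Unequal spread is plausible if music dampens the stress response in one arm. Skewness is plausible because LF/HF is a positive ratio. The protocol documents neither.

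**Working it through.** **1. The plan's own figure.** Inputs from section 10.1: difference 1.8, SD 2.3, two-sided 5%, power 90%.

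n per group = 2 × (1.960 + 1.282)² × 2.3² / 1.8² = 2 × 10.51 × 5.29 / 3.24 = 34.3, rounded up to 35.

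This matches the stated 35 and is a calculation for a difference in means. With the noncentral t distribution, power is 0.897 at 35 and 0.933 at 40 per group.

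**2. The rule as simulated.** Student's pooled t-test is used if Shapiro-Wilk passes in both arms and the F test passes; otherwise Mann-Whitney is used. The 0.05 cut-offs and per-arm normality tests are assumptions. In every row below the true mean changes are equal, with 40 per arm.

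Normal and same-shape scenarios (10,000 trials each; simulation standard error at 5% is √(0.05 × 0.95 / 10,000) = 0.2 points):

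| Scenario | Sent to Mann-Whitney | Rule rejects | Student | Welch |
|---|---|---|---|---|
| Normal, equal SD | 15% | 5.5% | 5.4% | 5.4% |
| Normal, SD ratio 1.5 | 73% | 5.2% | 5.1% | 5.0% |
| Normal, SD ratio 2 | 99% | 5.8% | 5.3% | 5.2% |
| Normal, SD ratio 3 | 100% | 7.1% | 5.2% | 5.0% |
| Skewed (log-normal, log-SD 0.75), identical in both arms | about 100% | 4.8% | 4.6% | 4.5% |

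With equal arms and normal data, Student's test itself holds close to 5% under unequal SDs. The variance check therefore moves the trial from a test that was adequate to one that is slightly worse.

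The F test is also a poor check under skewness. It rejects in 41% of trials in the last row, where the variances are equal.

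**3. Skewed change scores with unequal spread.** The endpoint is the change in LF/HF from before to during the injections, so the change was built as during minus before. Both values are log-normal and correlated 0.3 to 0.6 on the log scale. The main settings were baseline median 1.5, baseline log-SD 0.6 or 0.8, and during/before mean ratio 1.3, with 3,000 to 4,000 trials per setting.

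| Log-SD during injections, arm A vs arm B | Rule rejects | Welch |
|---|---|---|
| 0.8 vs 0.5 | 10–18% | 5–6% |
| 1.0 vs 0.5 | 23–41% | 6–7% |

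Nearly all of these trials end in Mann-Whitney.

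**4. Power for 1.8 / 2.3 at 40 per arm.** With equal SDs, simulated power is 0.934 for both Student and Welch. With SDs of 1.455 and 2.91 (average variance (2.12 + 8.47) / 2 = 5.29 = 2.3²), the rule has 0.906 and Welch 0.929.

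**The case against.** - **If music does nothing, the rule is sound.** Both arms then share one distribution and rejection stays near 5%. The higher rates require music to change the spread while leaving the mean change equal, so Mann-Whitney is detecting something real. This stands. The rates show that the test answers a different question from the one used for sizing. They are not false positives for an inert intervention.
- **The shapes are assumed.** Section 10.1 gives one SD, and nothing on skewness or unequal variance. This stands.
- **A reader might infer far larger errors.** Treating the change itself as a centred log-normal variable gives about 36% (log-SD 0.8 vs 0.5) and 72% (1.0 vs 0.5). A difference of two correlated skewed values is less skewed, so those figures do not describe this endpoint.
- **A reader might take the explicit switch as the stated primary rule.** It stands under secondary analyses. For the primary endpoint the switch is inferred from section 10.3, which offers no third test.
- **A reader might infer that Mann-Whitney rules out the promised confidence interval.** It does not: a Hodges-Lehmann shift or a probability of superiority comes with one. It would not estimate the 1.8-point mean difference.
- **Other analyses use a mean scale.** Section 10.4 allows a supplementary linear regression, and section 10.2 adds adjusted comparisons. They support the primary test but do not replace it.
- **Cut-offs can sit in the SAP.** This is fair for thresholds. But the protocol itself names the two tests and the variance check, and omits the option that would handle unequal variances.

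**Conclusion.** The point holds as a defect in how the primary test is fixed. The documents do not show that the trial's 5% error rate fails under no effect. The certain harm is that the primary question, a difference in means or in ranks, depends on the data and partly on judgement, while the sample size rests on a mean difference.

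The numerical harm depends on the data. It is nil when both arms share one distribution, and one to two percentage points for normal data with an SD ratio of 2 to 3. It is large (roughly 10–40% against 5–7% for Welch) only if the change is both skewed and unequal in spread. These figures rest on assumed 0.05 cut-offs and assumed distributions. The change should be made because it is cheap and concerns the one confirmatory test.

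**What to change.** In section 10.3, name one primary test without pre-testing: Welch's t-test on the change in LF/HF at injection visit 1, reported as the mean difference with its 95% CI. Remove Shapiro-Wilk and Fisher-Snedecor as grounds for choosing the test; they may remain descriptive. Report Mann-Whitney as a sensitivity analysis only. Apply the same wording to the visit 1 secondary endpoints and the other non-repeated continuous comparisons in section 10.4.

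Moving to log LF/HF would not be a like-for-like repair, because it no longer tests a 1.8-point difference. If that scale is preferred, it should be prespecified and the target difference restated.

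The cost is a wording change in two sections. It needs no new data and no change to the 40 per group.
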